#### Publicly available school suspensions and expulsions data

Using Local Education Agency codes for each case and control school obtained from the NCES, annual data on suspensions and expulsions, percentage of discipline outcomes tied directly to zero-tolerance policies, and the frequency of interactions between schools and local law enforcement will be directly downloaded from the Civil Rights Data Collection Website where data is available for all K-12 schools [35]. These data for each case and control school will be linked and used to comprise a “school discipline” summative score that includes the following indicators (accounting for school population size): number of in-school suspensions, out-of-school suspensions, and student expulsions. Other data (e.g., the number of students referred to law enforcement and number of school-related arrests) will also be collected from the Civil Rights Data Collection Website. Suspensions and expulsions are being considered as intervening outcomes stemming from both the implementation of school safety tactics and policies and the occurrence of shootings as a way to understand the role of student criminalization.

#### Other publicly available data on schools and their neighborhoods

Other publicly available data specific to the study schools, their neighborhoods (measured as census tracts and block groups), and their states are also being collected specific to each year of the study period and linked to each school and their school safety and discipline outcome data. These independent covariates are being collected via multiple data sources at the NCES and via US Census data. They include key variables at the school level: political orientation (as measured by voting patterns data obtained from US Census Bureau’s county-level Voting and Registration estimates), policies mandated by state government and insurance regulators (e.g., schools designated as gun-free zones), urban/non-urban (determined using NCES locale codes), economic (determined using percentage of students in each school eligible for free and reduced price lunches as well as residents below the poverty threshold in the surrounding neighborhood), and race/ethnicity (measured as differences in each school as well as among residents in the surrounding neighborhood). Additional covariates specific to the proposed study’s schools and their surrounding neighborhoods will include school staffing characteristics, school budget, student academic performance, and the school’s physical plant (e.g., outdoor play areas, number of floors).

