#### Control school ascertainment

Control schools are a randomly selected national sample of schools that have not experienced a shooting, by the definition described above and within the same time frame (1/1/2015–12/31/2023). Control schools are being obtained via random selection from a national database of public K-12 schools via the U.S. Department of Education’s National Center for Education Statistics (NCES). For each case school, one control school is being chosen as part of a stratified random sample and matched to each case school based on their geographic state, urban/non-urban status, and elementary/middle/high school status. State and urban/non-urban status will be determined using each school’s address and standard definitions of urbanicity taken from the NCES locale codes.

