### Data collection

Driven by preliminary study planning and statistical power calculations, the study protocol intends to collect data on an estimated 658 K–12 public schools (329 cases and 329 controls) across the US.

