#### Data analysis plan and study registration

An estimated 658 K-12 public schools will be included in our study sample. The presence or absence (binary 0–1 variables) of each of the 27 safety tactics and policies in case and control schools before each case school’s shooting will be statistically tested as independent variables of interest. The number of safety tactics and policies that each school has in place (from 0–27) will be statistically tested as independent count variables. And the number of suspensions and expulsions that have occurred will also be statistically tested as a proportion of the number of students in each school. Specific safety tactics and policies found to have small numbers will also be combined into groupings of safety tactics and policies as per prior aggregated categories: external target hardening, internal target hardening, student/staff monitoring, emergency procedures/drills, emergency notification technologies, medical support, and school security staff.

Analyses will begin with descriptive statistics to characterize cases and controls relative to independent variables. Categorical and continuous variables will be explored using frequency distributions, means, medians, standard deviations, skewness coefficients, and ranges. Bivariable analyses of predictor variables for each outcome will consist of t -tests, Chi-squared tests, and nonparametric comparison tests. Collinear independent variables will be identified using Spearman coefficients, tolerance statistics, and condition indices. As this population-based case-control study will be matched on state, urban/non-urban, and elementary/middle/high school status, conditional logistic regression model specifications will be used. The first two aims will adjust for confounders that will be methodologically and theoretically justified. The third aim will include interaction analyses with select effect modifiers: urban/nonurban, economic, and racial disparities. Despite having matched on these variables, effect modification analyses with these variables are possible and commonly conducted in case-control studies. Disparities analyses will include adjustments for sparse data. Researchers will reasonably limit the final group of predictor variables to promote statistical efficiency and provide the best unbiased estimators.

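### Political orientation is listed as a key covariate, but its named source, by title, covers voting and registration; no source of partisan direction is named, so political confounding may remain after adjustment

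*Protocol article*

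**What the plan says.** In the Protocol article, the section on other publicly available data on schools and their neighborhoods opens its covariate list with "They include key variables at the school level: political orientation" and fixes the measure in the same sentence: "political orientation (as measured by voting patterns data obtained from US Census Bureau’s county-level Voting and Registration estimates". On sources, the section says "These independent covariates are being collected via multiple data sources at the NCES and via US Census data". It names no election returns, party vote share, candidate choice or party registration.

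The section on the data analysis plan says "The first two aims will adjust for confounders that will be methodologically and theoretically justified". It does not list those confounders. Controls are "matched to each case school based on their geographic state, urban/non-urban status, and elementary/middle/high school status", and for this matched design "conditional logistic regression model specifications will be used".

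**The concern.** The article fixes both the construct and the instrument, and the two do not visibly match. Participation has no left-right direction: a county with high turnout or high registration can lean either way. Other covariates in the same sentence do fit their measures, such as lunch eligibility and neighbourhood poverty for economic status, or locale codes for urbanicity.

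The study is observational, so its conclusions rest on confounder control. Political lean is a plausible common cause of which tactics a school adopts (the abstract opens with arming teachers) and of local gun availability, hence shooting risk. The authors themselves list it as key. Matching on state and urbanicity leaves counties within a state free to differ in lean. What is at stake is a claim of adjustment for political orientation that the variable may not deliver, and odds ratios for politically patterned tactics that remain partly confounded.

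**Working it through.** **1. Construct against source.** The construct is political orientation. The source is titled Voting and Registration, at county level. The only hint of direction is the phrase voting patterns, which the article does not explain. Nothing in the text shows that the source yields partisan lean.

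**2. The article's own figure.** The planned sample is an "estimated 658 K–12 public schools (329 cases and 329 controls) across the US"; 329 + 329 = 658 agrees. The article gives no effect of political lean and no correlation between the source and lean, so everything below is a range under assumptions.

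**3. Unadjusted bias.** Assumptions, all within matching cells:
- The tactic has no effect (true odds ratio 1.00).
- Control lean is L ~ N(0,1).
- Lean multiplies the odds of a shooting by g per SD, so case lean is N(log g, 1).
- The tactic is present with probability expit(log t × L), that is, in half of schools at average lean.

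Then P0 = 0.5 by symmetry, P1 = E[expit(log t × (log g + Z))] with Z ~ N(0,1), and the matched-pair odds ratio is P1(1 − P0) / [P0(1 − P1)] = P1/(1 − P1). By numerical integration:

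| g = t | P1 | Apparent odds ratio |
|---|---|---|
| 1.2 | 0.5082 | 0.5082/0.4918 = 1.03 |
| 1.5 | 0.5395 | 0.5395/0.4605 = 1.17 |
| 2.0 | 0.6068 | 0.6068/0.3932 = 1.54 |

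Simulations of the same model gave about 1.04, 1.17 to 1.18 and 1.54 to 1.55, which agrees within simulation error. Adjusting for lean itself returned about 1.00.

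**4. What a proxy leaves.** Let r be the correlation of the proxy with lean and a the correlation of the tactic with lean, with the proxy independent of the tactic given lean. In the linear approximation, the share of bias left is (1 − r²)/(1 − a²r²). For example, r = 0.5 and a = 0.3 give 0.75/(1 − 0.09 × 0.25) = 0.75/0.9775 = 0.767.

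| r | a = 0.1 | a = 0.3 | a = 0.5 |
|---|---|---|---|
| 0 | 100% | 100% | 100% |
| 0.3 | 91% | 92% | 93% |
| 0.5 | 75% | 77% | 80% |
| 0.7 | 51% | 53% | 58% |

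Simulated conditional logistic fits for g = t = 1.5 and 2.0 gave about 91%, 77% and 53% at r = 0.3, 0.5 and 0.7.

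**5. Back to odds ratios.** The remaining log odds ratio is the share times the unadjusted log odds ratio. At a = 0.3:

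| Unadjusted | r = 0.3 | r = 0.5 | r = 0.7 |
|---|---|---|---|
| 1.03 | 1.03 | 1.03 | 1.02 |
| 1.17 | 1.16 | 1.13 | 1.09 |
| 1.54 | 1.49 | 1.39 | 1.26 |

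**6. Scale against precision.** With 329 complete pairs, the discordant counts are 329 × P1/2 and 329 × (1 − P1)/2, and SE = √(1/n10 + 1/n01). For P1 = 0.5395 these are 88.7 and 75.8, so SE = 0.156, and the unadjusted bias log 1.17 = 0.158 is about one standard error. The same sum gives about 0.2 standard errors at 1.03 (0.033/0.156) and about 2.7 at 1.54 (0.434/0.160).

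**The case against.** Several objections have weight.

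- **The source's contents are inferred.** The article does not describe what the estimates contain, and voting patterns could be read as how people vote. A reader might infer as settled fact that the source records only whether people vote or register. The documents do not say so; they support only that the title points to participation and that no directional source is named.
- **The size is not known.** A reader might also infer that political confounding would be left almost untouched. At least 90% remains only if r is about 0.3 or less; at 0.7 about half is removed. The strengths of confounding are assumed too, and at 1.2 per SD on both sides the bias is negligible.
- **Other controls help.** Matching on state with conditional analysis removes between-state political differences in Aim 1. State-mandated policies, poverty, lunch eligibility and race/ethnicity may carry some political information. The working places the assumed effects within matching cells, so state matching is already allowed for; the other covariates are not.
- **Aim 2 is not shown.** Nothing was calculated for suspensions and expulsions. The protection from matching carries over only if that analysis also conditions on the pairs.
- **Use in the model is not fixed.** The adjustment set is not listed, and an article may properly leave it to the full plan.
- **The level label is minor.** The variable is placed among school-level ones, but the same sentence says county-level.

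All of these limit the size or certainty of the harm. None removes the mismatch: no other listed covariate measures lean directly, and the choice of source is stated in the article itself.

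**Conclusion.** The point holds as a mismatch between a named construct and its named source. If the variable is used as described, the study may say it adjusted for political orientation when the variable has no evident partisan direction, and confounding by lean within state and urbanicity strata may remain in Aim 1. For Aim 2 this is possible but was not examined.

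The harm runs from negligible to material: a null tactic would show about 1.03 to 1.54 before adjustment, with about half to all of that bias left for a proxy correlation of 0.7 down to 0. The range rests on the assumed effects of lean, a tactic prevalence of one half at average lean, a proxy unrelated to the tactic given lean, and no help from other covariates. It does not show that the study's odds ratios will be wrong by any particular amount. The change is worth making because it is cheap and data collection is still under way.

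**What to change.** In the covariate list, measure political orientation with a variable that has partisan direction and name its source. One suitable choice is the two-party vote share in the school's county, from public election returns for the last presidential election before the exposure school year. Label it county-level. If the Voting and Registration variable is kept, call it voter participation and do not count it as adjustment for political orientation. If the authors hold that the present source does give partisan direction, they should name the exact variable.

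The cost is one extra public data linkage by county and a one-line correction to the covariate description, repeated wherever the registered plan carries the same wording. No field work is needed. County vote share remains an area measure and will not capture differences in lean within a county.

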### Protection of human subjects

The large majority of data collected in this study do not involve human subjects. Indeed, much of the data collected in this study are publicly available. In the case that a school’s safety plan for a specific academic year of interest is not available online, the study directors are emailing the district’s superintendent of the school directly to inquire if they would be willing to provide a copy of the safety plan for the purpose of this research study. As a result, the superintendent of every participating school district in this proposed work is eligible for participation, but no identifying or private information about the superintendents themselves will be recorded.

Approval for this study was obtained from the Columbia University Human Research Protection Office and Institutional Review Board in November 2021 (IRB protocol number: AAAT9087). The study was deemed exempt from the requirement of obtaining written or oral consent.

### Data organization and management

#### Study design

The case-control study design is a natural choice in accomplishing the aims proposed here given the relatively rare outcome of school shootings and the need to quantitatively test school safety tactics and policies by including a national comparator group of control schools that have not experienced shootings. In addition, other study designs, such as randomized controlled trials or cohort studies, would be unethical to conduct or would take infeasibly long periods of time to complete, thus underscoring the benefits of utilizing the case-control study design as described here.

Per the study’s Specific Aims, this study is examining associations between safety tactics/policies and various outcomes (Fig 1). As described in Specific Aim 1, our research team is testing relationships between the total number and specific presence of 27 school safety tactics and policies using a case-control design to calculate the odds of intentional school shootings. In Specific Aim 2, we are testing the relationships between the total number and specific presence of 27 types of school safety tactics and policies and the occurrence of school suspensions and expulsions. Aims 1 and 2 are possible due to the temporal specificity of the data, as implementation of safety tactics/policies and occurrence of school shootings and suspensions/expulsions are date stamped.

**Fig 1 pone.0302622.g001:**
[figure not shown]
Conceptual framework and temporality of the proposed case-control study.

In addition, our research team is exploring whether implementation of school safety tactics and policies prompts the occurrence of school suspensions and expulsions, which may then potentially lead to the occurrence of later school shootings. Some school shooters had been previously expelled or had a history of being suspended. Certain security tactics/policies may increase suspensions/expulsions, which can then affect school shootings. Aim 3 further delineates these potential relationships in terms of urban/non-urban, economic, and racial subgroups. This final aim is key to understanding how various relationships among safety strategies, suspensions/expulsions, and shootings play out for different populations and where school districts and policymakers may best and most effectively focus their safety efforts.

#### Data analysis plan and study registration

An estimated 658 K-12 public schools will be included in our study sample. The presence or absence (binary 0–1 variables) of each of the 27 safety tactics and policies in case and control schools before each case school’s shooting will be statistically tested as independent variables of interest. The number of safety tactics and policies that each school has in place (from 0–27) will be statistically tested as independent count variables. And the number of suspensions and expulsions that have occurred will also be statistically tested as a proportion of the number of students in each school. Specific safety tactics and policies found to have small numbers will also be combined into groupings of safety tactics and policies as per prior aggregated categories: external target hardening, internal target hardening, student/staff monitoring, emergency procedures/drills, emergency notification technologies, medical support, and school security staff.

Analyses will begin with descriptive statistics to characterize cases and controls relative to independent variables. Categorical and continuous variables will be explored using frequency distributions, means, medians, standard deviations, skewness coefficients, and ranges. Bivariable analyses of predictor variables for each outcome will consist of t -tests, Chi-squared tests, and nonparametric comparison tests. Collinear independent variables will be identified using Spearman coefficients, tolerance statistics, and condition indices. As this population-based case-control study will be matched on state, urban/non-urban, and elementary/middle/high school status, conditional logistic regression model specifications will be used. The first two aims will adjust for confounders that will be methodologically and theoretically justified. The third aim will include interaction analyses with select effect modifiers: urban/nonurban, economic, and racial disparities. Despite having matched on these variables, effect modification analyses with these variables are possible and commonly conducted in case-control studies. Disparities analyses will include adjustments for sparse data. Researchers will reasonably limit the final group of predictor variables to promote statistical efficiency and provide the best unbiased estimators.

Multiple testing in regression models will be handled by pre-specified variable selection procedures (Benjamini-Hochberg) to control false positive findings in terms of type I error rate and false discovery rate. Several regression models will be tested and compared using Wald statistics, and multiple testing adjustments and false discovery rates accounting for correlated conditions and dependency will also be used to provide appropriate estimates of statistical significance and statistical inference. Our research team has pair-matched to increase efficiency in a situation where the distributions of the matching covariates are drastically different in case and control populations. We will use a double robust, efficient, weighted targeted maximum likelihood procedure for the estimation of causal parameters in matched case-control study designs. Where missing data do exist and are missing at random, researchers will use multiple imputation.

Lastly, in line with best practices regarding data storage and in order to assure research quality and integrity, we will implement processes to maximize the rigor, reproducibility, and generalizability of our proposed study. Openness and transparency are being facilitated by pre-registering our planned methods, analyses, and covariates, and sharing of computer code, datasets, and research results. To reduce the likelihood of any possible publication or confirmation biases that might be skewed towards positive results, primary analyses and hypotheses involving tests of the school tactics and policies specified in our specific aims have been publicly pre-registered via clinicaltrials.gov. We will also take every care to ensure that relevant alternative arguments are considered when presenting our results. This will offer school districts and policymakers at the state and federal levels a sound evidence base for the development of fair, objective, and evidence-based policies.

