## Methodology

### Sampling frame

National data from a random sample of K-12 public schools around the US are being collected for this case-control study. Case schools are being ascertained through a comprehensive review of multiple national school shooting databases, including the K-12 School Shooting database, the Everytown for Gun Safety database on gunfire on school grounds, and the Washington Post database on school shootings, to identify all schools that have experienced an intentional gunfire against others on the campus during school hours. Control schools will be ascertained via random selection from the US department of Education’s national database on all K-12 schools and matched to case schools in 1:1 ratio. The full set of inclusion and exclusion criteria developed by the study team are included [S1 File].

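### The bivariable comparisons by shooting status name tests that do not use the 1:1 pairs, so their p-values are likely to be conservative and may disagree with the unadjusted conditional models

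*Protocol article*

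**What the plan says.** Under Sampling frame, the protocol article says that controls are "matched to case schools in 1:1 ratio". Under Control school ascertainment, each control is "matched to each case school based on their geographic state, urban/non-urban status, and elementary/middle/high school status". The section on the independent variable adds that tactics in both schools of a pair are read for the school year before the case school's shooting, so the pair also shares calendar time. The planned size is "an estimated 658 K–12 public schools (329 cases and 329 controls) across the US".

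Data analysis plan and study registration sets out the analysis in this order:

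- Description: "Analyses will begin with descriptive statistics to characterize cases and controls relative to independent variables".
- Bivariable step: "Bivariable analyses of predictor variables for each outcome will consist of t -tests, Chi-squared tests, and nonparametric comparison tests".
- Regression for the matched data: "conditional logistic regression model specifications will be used", with the matching given as the reason.
- A further estimator designed for matching: a "weighted targeted maximum likelihood procedure for the estimation of causal parameters in matched case-control study designs".

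The matching is used in the last two steps. It is not mentioned in the bivariable step.

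**The concern.** Shooting status is one of the outcomes covered by the bivariable sentence, and for that outcome the data are pairs. State mandates, urban practice, school level and calendar year can all make the two schools of a pair alike in the tactics they use. A chi-squared test as ordinarily understood treats the 658 schools as independent, and so does a two-sample t-test. With positive within-pair correlation, the variance of the case-control difference is then overstated and the p-values are too large.

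What is at stake is the unadjusted comparison of the 27 tactics, their count and the covariates. Its p-values would lean towards no difference, and for the same variable they could disagree with a conditional logistic model containing that variable alone. Readers would have two unadjusted answers from one dataset, only one of which respects the design.

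**Working it through.** **Inputs from the article.** Matching is 1:1, with 329 cases and 329 controls. The stated total reproduces: 2 × 329 = 658. The article gives no significance level, power, effect size, exposure prevalence or within-pair correlation, so the calculation behind 658 cannot be repeated and the correlation has to be taken over a range.

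**Formula.** With equal variances σ² and within-pair correlation ρ, the true variance of the mean case-control difference over n pairs is 2σ²(1 − ρ)/n. An independent-sample test uses 2σ²/n. Hence:

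- SE used / true SE = 1/√(1 − ρ)
- actual size of a nominal 5% two-sided test = 2Φ(−1.96/√(1 − ρ))

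For binary tactics, ρ is the phi coefficient within pairs. Putting the numbers in:

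- phi 0.05: 1/√0.95 = 1.03; size 2Φ(−2.01) = 4.4%
- phi 0.16: 1/√0.84 = 1.09; size 2Φ(−2.14) = 3.2%
- phi 0.39: 1/√0.61 = 1.28; size 2Φ(−2.51) = 1.2%

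**Simulation for binary tactics.** Assumptions: 329 pairs, 8,000 replicates per setting, control exposure logit centred on 30%, between-pair SD of 0, 0.5, 1 or 2 on the logit scale, two-sided 5% level, and a conditional odds ratio of 1 (size) or 1.5 (power). The Monte Carlo standard error at 5% is √(0.05 × 0.95/8000) = 0.24 percentage points.

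| Logit SD | phi | SE ratio | Chi-squared size | McNemar size | Chi-squared power, OR 1.5 | McNemar power, OR 1.5 |
|---|---|---|---|---|---|---|
| 0 | 0.00 | 0.99 | 5.3% | 5.2% | 0.70 | 0.69 |
| 0.5 | 0.05 | 1.03 | 4.2% | 4.8% | 0.65 | 0.67 |
| 1 | 0.16 | 1.08 | 3.3% | 5.1% | 0.56 | 0.63 |
| 2 | 0.39 | 1.27 | 1.3% | 5.1% | 0.31 | 0.51 |

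Formula and simulation agree. McNemar holds its size throughout. In the last three rows, breaking the pairs costs about 0.02, 0.07 and 0.2 in power. McNemar's own power also falls down the table, because more alike pairs leave fewer discordant ones, so the fair comparison is within a row.

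**Counts and continuous covariates.** By the same formula, an independent-sample t-test at ρ = 0.1, 0.3 and 0.5 uses a standard error 1.05, 1.20 and 1.41 times the correct one. These correlations are also assumed.

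**The case against.** The strongest reply is that the article never says unpaired. The named tests are families that include the paired t-test, McNemar's test and the signed-rank test. The sentence covers each outcome, including suspensions and expulsions, where the comparison is not between the case and the control of a pair. A condensed article may also leave the exact form to the analysis plan.

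Part of this stands: the independent-sample reading is an inference, though the ordinary one. A chi-squared test named without qualification for binary exposures is normally the test of independence, and the text brings in the matching only two sentences later, for the regression. The article does name its tests, so asking for the paired forms corrects a stated choice and does not merely ask for absent detail.

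It is also fair that the size of the effect is unknown. The Introduction reports lockdown drills at 96% of schools and cameras at more than 80%. For a tactic at 96% prevalence, a logit SD of 1 implies phi of only about 0.05, where the loss is small. The error is conservative and creates no false positives.

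Two stronger readings are tempting but not supported:

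- **Attenuated study odds ratios.** A crude odds ratio from the unmatched table would shrink towards 1 (1.46 to 1.28 for a true 1.5 over the same range of phi). The article plans no such estimate. Its odds ratios for shootings come from conditional logistic regression.
- **Predictors screened out.** The article says that the final set of predictors will be limited, but nowhere that bivariable p-values will do this. It says that confounders will be justified on methodological and theoretical grounds, and it places variable selection within the regression models, using Benjamini-Hochberg.

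**Conclusion.** The point holds as a minor one, confined to the preliminary comparisons by shooting status. As worded, that step does not use the pairs that the design creates. In the usual form of the named tests, its p-values are conservative whenever matching induces positive within-pair correlation.

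The size runs from negligible at phi near 0.05 to substantial at phi near 0.39. It rests on three assumptions: the independent-sample reading, a range of correlations that has no source in the article, and control exposure centred on 30%. With no within-pair correlation there is no loss. The conditional logistic and matched-design targeted maximum likelihood estimates do not depend on this step and stand as planned. The Aim 2 discipline outcomes are outside the point.

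**What to change.** In Data analysis plan and study registration, split the bivariable sentence by outcome. For comparisons by shooting status, state that:

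- the 27 binary tactics are compared with McNemar's test or univariable conditional logistic regression, with discordant-pair counts shown;
- counts and continuous covariates are compared with paired t-tests or Wilcoxon signed-rank tests.

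The cost is a change of wording in the analysis plan. No new data are needed, and the article reports that data collection is still under way, so the change can be made before analysis. Only the preliminary p-values would change.
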